### Effectiveness Outcomes

To measure the effectiveness of ECEM-TZ, the following will be assessed:

Newborn care knowledge: Knowledge will be assessed using a modified questionnaire developed by McConnell and colleagues [22] assessing newborn care knowledge. The questions determine whether mothers can identify danger signs, handwashing practices, cord care, newborn thermal care, and breastfeeding. A total sum of the number of items mothers can identify will be created. Additionally, binary variables will be created to determine whether mothers can identify three or more newborn danger signs, two or more best practice hand washing, two or more cord care practices, three or more thermal care practices, and two or more breastfeeding practices. Based on these variables, a summative score will be created ranging from 0 to 5, with a higher score representing increased newborn care knowledge.Maternal self-efficacy: Parenting self-efficacy will be measured using the Karitane Parenting Confidence Scale [20]. This 15-item scale was developed to assess the perceived self-efficacy of mothers of newborns from birth to aged twelve months and has acceptable internal consistency (Cronbach α=0.81) and test-retest reliability (*r*=0.88) [20]. A cutoff score of 39 or less (out of a possible 45) was determined to be a clinically low perceived parenting self-efficacy [20]. The Kiswahili version was piloted as part of the development phase.Breastfeeding self-efficacy: Breastfeeding self-efficacy will be measured using the Breastfeeding Self-Efficacy Scale—Short Form [23]. This 14-item tool was developed originally in Canada and has been translated into Kiswahili and determined to be valid and reliable [24]. Higher scores indicate higher breastfeeding self-efficacy.Postpartum depression: Depression will be measured using the Edinburgh Postnatal Depression Scale (EPDS) [25]. The EPDS is a self-report screening scale with 10 items that can indicate if a respondent has symptoms related to perinatal depression [25,26]. The EPDS is valid for assessing depressive symptoms across the perinatal period with a score >12 considered as high symptoms of depression. The EPDS has been used in a variety of African countries to measure perinatal depression [27-29]. The EPDS has already been translated into Kiswahili and has been modified for contextual differences [30].Postpartum anxiety: Anxiety will be measured using the Generalized Anxiety Disorder (GAD)-7 [31], which is a 7-item scale used to assess GAD. The scale ranges between 0 and 21, with scores of 10 or greater indicative of generalized anxiety at a moderate or severe level. The GAD-7 has already been translated into Kiswahili [32] and has been widely used to measure perinatal anxiety in African countries, including in Tanzania [33,34].Newborn morbidity and mortality: The 6-week follow-up survey will collect information on morbidity (eg, diarrhea, jaundice, or infection), need for readmission due to illness, and mortality.Postnatal clinic attendance at six weeks: The 6-week follow-up survey will collect information on the number and date of postnatal contacts.

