### Sample Size

The sample size was calculated based on the outcome of newborn care knowledge. While previous studies on postnatal education knowledge are significantly varied and no studies to date have reported on maternal postnatal education knowledge in Tanzania, we considered a binary summative score of 100% as the goal at 6 weeks post partum. Using a power of 80%, α of .05 (2-tailed), and assuming 90% of the intervention group and 70% of the control group will score 100% at 6 weeks, a total sample size of 124 is required. This is in line with our implementation sample size approach: recruiting across two hospitals to determine the feasibility of recruitment at these sites. We will aim for approximately similar numbers of participants at each site, recruiting for six weeks. Assuming two research assistants are recruiting five days per week at each hospital and each research assistant can recruit a minimum of 2 participants per day, this would be approximately 20 participants per week. Over six weeks, this would be 120 participants we anticipate recruiting. If recruitment is higher than anticipated, it will be limited to a maximum of 200 across both sites.

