### Statistical Analysis

Data will be analyzed on an intention-to-treat (ITT) analysis basis as well as per protocol analysis (excluding women who requested to stop the program or were lost to follow-up). Data will be analyzed using SPSS (version 29, IBM SPSS Statistics, IBM Corporation). Demographic characteristics will be expressed in means, SDs, and percentages, as applicable, based on group allocation. Any significant differences in baseline characteristics, examined through a chi-square analysis or Mann-Whitney test, will be adjusted for in the analyses. A *P* value of .05 will be considered significant for all outcomes. For all analyses, unadjusted and adjusted models will be reported.

For the effectiveness outcomes, total and summative scores will be reported using means, SDs, and percentages, as appropriate. Analysis of covariance will be used to measure whether scores differ between the two groups, adjusted for the pretest scores and any significant baseline characteristics. For newborn care knowledge, newborn morbidity, newborn mortality, and attendance at postnatal care six-week contact, binary variables will be created, and data will be analyzed using logistic regression.

For the implementation outcomes, descriptive statistics will be used to describe mothers’ experience with ECEM-TZ and outcomes will be reported using means, SDs, and percentages, as applicable. Open-ended questions will be analyzed using thematic analysis [35]. Responses will be transcribed verbatim and translated into English for analysis.

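### P=.05 is declared significant for every outcome, and the one test that sized the trial is never made the decisive one

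*Protocol article*

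**What the plan says.** **Outcomes.** The Effectiveness Objectives and Effectiveness Hypotheses put eight outcomes into one objective and one hypothesis: knowledge, parenting self-efficacy, breastfeeding self-efficacy, depression, anxiety, postnatal attendance, newborn morbidity and newborn mortality. None is called primary.

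**Knowledge scorings.** Under Effectiveness Outcomes, "A total sum of the number of items mothers can identify will be created". Five domain pass/fail variables follow, and from these "a summative score will be created ranging from 0 to 5". The Sample Size section adds a further form: "we considered a binary summative score of 100% as the goal at 6 weeks post partum".

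**Sizing.** The calculation uses 80% power and a two-tailed alpha of .05, "assuming 90% of the intervention group and 70% of the control group will score 100% at 6 weeks", and concludes that "a total sample size of 124 is required".

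**Analysis.** The Statistical Analysis section applies ANCOVA to scores, and logistic regression to binary variables for knowledge, morbidity, mortality and attendance. It does not say which knowledge variable decides. ITT and per-protocol analyses are both planned and neither is ranked. "For all analyses, unadjusted and adjusted models will be reported", again unranked. Covariates are the pretest score (for ANCOVA) plus any baseline characteristic that differs significantly between arms. The threshold sentence is that a P "value of .05 will be considered significant for all outcomes".

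**The concern.** An alpha of .05 in a sample size calculation is the error rate of one test. Here that test is the binary 100% knowledge score. The analysis section does not carry it forward. It gives the same threshold to every outcome, so a result below .05 on another outcome or another knowledge scoring has the same declared standing as the test the trial was built on.

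The practical risk lies in the effectiveness claim. The Discussion anticipates a significant gain in knowledge without saying on which measure. A positive item count or 0-5 score could be reported as confirming the hypothesis even if the 100% score showed no difference.

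**Working it through.** **Inputs from the article:** 90% versus 70% scoring 100%; two-sided alpha .05; power 80%; 1:1 allocation; eight effectiveness outcomes; .05 for each; 71 control and 72 intervention mothers recruited. The article gives no correlations between outcomes, so those below are assumptions.

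**1. The plan's own figure.** Two proportions, pooled variance under the null, no continuity correction:

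n per arm = [1.960 × √(2 × 0.80 × 0.20) + 0.8416 × √(0.90 × 0.10 + 0.70 × 0.30)]² / 0.20²
= (1.1087 + 0.4610)² / 0.04 = 61.6, rounded up to 62, so 124 in total.

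The stated 124 is reproduced, with power 80.3% at 62 per arm. It is the size for one test at .05.

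**2. Eight outcomes, each tested once, no true effect, independent.** 1 − 0.95⁸ = 33.7%. Mortality will have few events and its test can add little. Leaving it out gives 1 − 0.95⁷ = 30.2%.

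**3. The same eight, correlated.** Test statistics were simulated as z_j = √ρ·c + √(1−ρ)·e_j, with c and e_j standard normal and 250,000 replicates, counting any |z_j| > 1.96:

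| Assumed ρ | Chance of at least one P<.05 |
|---|---|
| 0 | 34% |
| 0.3 | 30% |
| 0.5 | 25% |
| 0.7 | 19% |

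**4. Alternative scorings and versions.**
- Counting three overall knowledge scorings (item total, 0-5 score, 100% binary) in place of one makes ten tests. The chance is 40% if independent (1 − 0.95¹⁰). It is about 34% to 39% with assumed correlations of 0.5 to 0.7 among the knowledge scorings and 0 to 0.3 otherwise.
- Running the eight outcomes in four versions (ITT or per protocol, unadjusted or adjusted), with versions of the same outcome assumed correlated at 0.95, gives about 49%, 44% and 37% at between-outcome correlations of 0, 0.3 and 0.5. The matching single-version figures are 34%, 30% and 25%.

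**5. What naming one test achieves.** The type I error of the primary claim returns to 5%, at 124 in total with 80.3% power. Power is about 85% at 71 per arm, before dropout. If all eight outcomes stayed co-equal under Bonferroni, each would be tested at .05/8 = .00625. The same 90% versus 70% contrast would then need 202 mothers, with power of 52% at 62 per arm and 60% at 71.

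**The case against.** **The lead outcome is evident, and the rest belongs in the full protocol or SAP.** The trial is sized on the 100% knowledge score, and knowledge is listed first throughout. An article may well leave formal labels and multiplicity rules to a fuller document. Part of this stands: the sample size does point to one outcome, which is why the repair is small. But the article is not silent on the threshold. It states a rule for all outcomes, and a hierarchy in an SAP would have to contradict that rule.

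**A reader might infer that a false positive is likely, or count dozens of tests.** Treating 16 knowledge and other variables as independent gives 1 − 0.95¹⁶ = 56%, and four versions of each make 64 P values. The article does not support that reading. The five domain variables are components from which the 0-5 score is built, and the text does not say each will be tested. The scorings overlap, and the four versions are near-duplicates of one comparison. For eight outcomes tested once, the figure is about one in three or less.

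**A reader might also infer that the binary score wastes data and that a knowledge score should replace it.** Reading 70% versus 90% as a cut on one normal score gives d = 1.2816 − 0.5244 = 0.757 and 28 per arm. But the 0-5 score counts passes on five domain cut-offs, with 70% to 90% of mothers expected at the maximum. With five equally difficult, independent domains, pass rates are 0.70^(1/5) = 0.931 and 0.90^(1/5) = 0.979. The mean difference is 5 × 0.048 = 0.240 and the SD about 0.46, so d ≈ 0.52. At assumed domain correlations up to 0.5, d is 0.50 to 0.52. That needs 58 to 64 per arm, essentially no gain over 62. For the item total the article gives no SD or range, so no figure can be derived.

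A switch would also be unsafe now. The Randomization, Allocation, and Blinding section says the researchers know the allocation, and follow-up finished on September 21, 2024.

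**Conclusion.** The point holds. The stated .05 rule, applied to eight unranked outcomes with unranked scorings, analysis sets and models, does not protect the 5% error rate on which the trial was sized. With no true effect, the chance of at least one P<.05 over the eight outcomes tested once is about 34% under independence, and about 19% to 30% at assumed correlations of 0.7 to 0.3. Mortality's sparse events make these figures slightly high, while extra scorings and versions push them up. The sample size of 124 is not in error.

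Calling the adjusted analysis primary would not be enough on its own. As written, its covariates depend partly on which baseline tests turn out significant, so the model would still be chosen by the data.

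**What to change.** Before any outcome analysis, replace the threshold sentence in the Statistical Analysis section with:

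> The primary analysis is the binary 100% knowledge score at T2, in the ITT population, by logistic regression adjusted for prespecified covariates (T1 knowledge and site), at two-sided .05. All other outcomes and knowledge scorings are secondary, reported with confidence intervals and without confirmatory significance claims (or with Holm adjustment). Unadjusted and per-protocol results are sensitivity analyses.

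State which form of T1 knowledge enters the model. Site is the randomization stratum and T1 knowledge is collected at baseline (Table 1), so both are available. Baseline significance tests should no longer choose covariates for the primary model.

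The right deadline is outcome analysis, not unblinding, because the researchers already know the allocation. The Figure 1 caption says that analysis was not yet complete, so the article leaves room for the change. It needs no further participants and no change to the 124. The small downside is that some secondary results can no longer be called significant.

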## Introduction

### Background

The postnatal period during the first 6 weeks of life is a critical time point for newborns and mothers in Tanzania, which has a neonatal mortality ratio of 20 per 1000 live births [1] and a maternal mortality ratio of 104 per 100,000 live births [2]. Neonatal and maternal mortality is highest in the first week post partum [3,4]. Despite the high number of deaths that occur postnatally, most mothers and their newborns receive insufficient care during this period, especially in low- and middle-income countries (LMICs) [5]. There is a significant need to develop and evaluate innovative approaches to reach mothers during this period to ensure they are knowledgeable and confident in caring for their newborns at home.

While most Tanzanian women (90%) have at least 1 antenatal care contact, only half (51%) of the women and 54% of the infants receive postnatal care within 2 days after giving birth [2]. Further, health facilities are often unable to provide individualized education based on maternal needs due to staff shortages and resource constraints [6-8]. Across Tanzania, mothers receive little education about how to care for their newborns before hospital discharge due to significant health system challenges [6,8,9].

One innovative strategy that can be used to provide postnatal education directly to parents is mobile health (mHealth) [10]. The goal of mHealth interventions delivered postnatally is not to replace the need for in-person follow-up but to complement existing care and fill knowledge gaps by providing timely, standardized, relevant, and evidence-based information on newborns’ care at home. The use of mobile phones to reach mothers is supported by the World Health Organization recommendations, which state that traditional postnatal contact can be enhanced through mobile phone–based contact between mothers and the health system [11].

Due to the severe shortage of health care providers and the low rate of in-person postnatal contacts in Tanzania [12], Essential Coaching for Every Mother Tanzania (ECEM-TZ) is poised to bridge this gap without adding a significant burden to the health system. The goal of the ECEM-TZ intervention is to improve maternal access to knowledge during the immediate 6-week postnatal period, and to increase maternal self-efficacy and improve mental health outcomes.

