### Effectiveness Hypotheses

Mothers who receive ECEM-TZ will have higher levels of newborn care knowledge, maternal parenting self-efficacy, breastfeeding self-efficacy, and postnatal care attendance and lower rates of postpartum depression symptoms, anxiety symptoms, and newborn morbidity and mortality at 6 weeks post partum in comparison to those who received standard postpartum care.

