### Inclusion Criteria

Mothers are eligible if they meet the following criteria: (1) have given birth within the past 48 hours, (2) have daily access to a mobile phone with text messaging capabilities, (3) are aged older than 18 years, and (4) speak and read English or Swahili. Participants will be excluded if (1) newborns die or are expected to die before leaving the hospital; (2) they have no access to a mobile phone, either personal or shared; (3) they are unwilling to receive SMS messages; (4) decline to participate; (5) are experiencing major postnatal complications expected to impact learning or ability to consent while in the hospital (eg, postpartum hemorrhage or seizures); or (6) participated in ECEM-TZ development phase.

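### Newborn mortality is assigned to logistic regression with about 2.9 deaths expected in total, so the odds ratio will often not be finite and the mortality hypothesis has almost no power

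*Protocol article*

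**What the plan says.** The Statistical Analysis section names the method: for newborn care knowledge and also "newborn morbidity, newborn mortality, and attendance at postnatal care six-week contact, binary variables will be created, and data will be analyzed using logistic regression". Two further rules there cover every outcome. One sets a P value of .05 as the threshold. The other reads "For all analyses, unadjusted and adjusted models will be reported". On covariates it says: "Any significant differences in baseline characteristics, examined through a chi-square analysis or Mann-Whitney test, will be adjusted for in the analyses".

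The Effectiveness Hypotheses section gives mortality a direction, predicting that mothers who receive the messages will have "lower rates of postpartum depression symptoms, anxiety symptoms, and newborn morbidity and mortality at 6 weeks post partum". The Discussion repeats that expectation.

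The only newborn death rate in the article is in the Background, a "neonatal mortality ratio of 20 per 1000 live births". Under Inclusion Criteria, mothers are excluded if "newborns die or are expected to die before leaving the hospital". The Sample Size section rests on newborn care knowledge alone and concludes that "a total sample size of 124 is required". The Results section reports 143 recruited, 71 control and 72 intervention. The article does not call mortality descriptive, names no method for sparse events, and does not list the point among its limitations.

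**The concern.** Maximum-likelihood logistic regression on treatment arm gives a finite odds ratio only if both arms contain at least one death and at least one survivor. With two or three deaths expected in the whole trial, an empty arm is a common outcome. The problem also grows with benefit: the better the intervention works, the more likely its arm has no deaths and the less likely the prescribed estimate exists.

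This is more than low power in a secondary outcome. The article itself fixes the model, requires an unadjusted and an adjusted version, and applies a significance threshold. Followed as written, the rule can yield an infinite or zero odds ratio with an uninformative P value, or a non-significant result that says almost nothing about a stated hypothesis.

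**Working it through.** **Inputs.** Mortality 20 per 1000 = 0.02 (Background). Arms of 71 and 72 (Results). Planned total 124, from 90% vs 70%, 80% power, two-sided alpha .05 (Sample Size). The rates of 1% and 3% are assumptions used to show the range. One newborn per mother and complete follow-up are also assumed.

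**The plan's own figure.** The two-proportion formula with pooled variance and no continuity correction gives:

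n per arm = [1.960·√(2·0.8·0.2) + 0.842·√(0.9·0.1 + 0.7·0.3)]² / 0.2² = 61.6, rounded up to 62.

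The total is 124, so the figure reproduces. It concerns knowledge only; the article states no event count or power for mortality.

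**Expected deaths with no effect.** 143 × 0.02 = 2.86 in total. At the planned size, 124 × 0.02 = 2.48.

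**Chance that at least one arm has no deaths.** With control risk p0 and intervention risk p1:

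P = (1−p0)^71 + (1−p1)^72 − (1−p0)^71·(1−p1)^72

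At 2% in both arms: 0.2383 + 0.2335 − 0.2383·0.2335 = 0.416. At 2% vs 1%: 0.2383 + 0.4850 − 0.2383·0.4850 = 0.608.

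| Control risk | No effect | Mortality halved |
|---|---|---|
| 1% (assumed) | 74% | 85% |
| 2% (article) | 42% | 61% |
| 3% (assumed) | 21% | 41% |

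At 2% with no effect, there are no deaths in either arm with probability 0.2383·0.2335 = 6%.

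**Power for 2% vs 1% at 71/72.** All 2×2 tables were enumerated, weighted by their binomial probabilities, and those with P ≤ .05 summed.

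- Wald test of the log odds ratio, counting an empty arm as non-significant: 0.003%. The article does not name the test; Wald is assumed as the usual companion of a logistic odds ratio.
- Fisher's exact test: 0.7%.
- Chi-square test: 2.8%.

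With no deaths in the intervention arm, Fisher's test needs 5 control deaths to reach .05 (P = .028; 4 deaths give P = .058). Five exceeds the total expected.

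**Size needed for a halving.** The same formula gives:

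[1.960·√(2·0.015·0.985) + 0.842·√(0.02·0.98 + 0.01·0.99)]² / 0.01² ≈ 2,319 per arm, or 4,638 in total.

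**Adjusted model.** Adding covariates leaves separation at least as likely as in the unadjusted model.

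**The case against.** Mortality does not set the sample size, and the article claims no power for it. At 2% with no effect, both arms have deaths in 58% of trials, so a finite unadjusted odds ratio exists more often than not. The Wald test errs on the safe side: with no effect it rejects in about 0.007% of trials, so a false mortality claim from it is very unlikely. Covariates enter only if baseline characteristics differ significantly, and there may be none. Percentages are promised as appropriate, so risks by arm may appear anyway. Handling of separation is often left to an analysis plan, which is not shown here.

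These points limit the weight of the concern but do not remove it. The article does not leave the method open; it names one that fails in a large share of the plausible outcomes.

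Three stronger readings are tempting and go too far:

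- **That three deaths is a ceiling, or that mortality cannot be tested at all.** The 2.86 is an expectation; at 2%, more than three deaths occur with probability 32%. An exact test can always be computed; it has almost no power. The national neonatal rate may also not fit these two hospitals, and it does not cover the last two weeks of follow-up.
- **That newborn morbidity has the same defect.** The article gives no morbidity rate and does not say that morbidity will be modelled item by item, so nothing supports this.
- **That the both-models rule should be withdrawn throughout.** For the other outcomes it guards against selective reporting.

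**Conclusion.** The point holds for mortality alone. On the article's own rate and the numbers recruited, the prescribed model has a 42% chance of giving no finite odds ratio if there is no effect and a 61% chance if mortality is halved. Whichever of the three tests is used, power for a halving is below 3%. The main uncertainty is the death rate after discharge. Excluding deaths before discharge pushes it below 2%, since the Background says mortality peaks in the first week; the 6-week window pushes slightly the other way. Across 1% to 3% the chance of failure varies widely, but at no point in that range does the model become a sound choice. Losses to follow-up would only reduce the number of deaths observed.

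This is a change worth making, not a threat to the trial. The knowledge comparison that determines the sample size does not depend on it.

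**What to change.** For newborn mortality only:

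- Replace logistic regression with the number of deaths and the risk in each arm, and an exact confidence interval for the risk difference.
- Exempt mortality from the sentence requiring unadjusted and adjusted models, and keep that sentence as it stands for all other outcomes.
- Keep the mortality hypothesis, but label it unpowered and descriptive, with no significance claim.
- Disclose the timing. Follow-up ended on September 21, 2024, the researchers know allocation, and the CONSORT figure caption says analysis was not yet complete. The change should be recorded as made after follow-up and, if still true, before the mortality data were analyzed.

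The cost is a wording change, a disclosed departure from the published method, and the loss of a formal mortality test that has almost no power.

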### Randomization, Allocation, and Blinding

Using a 1:1 allocation, participants will be randomized into either the intervention or control group using a computer-generated stratified block randomization with blocks varying between 4 to 8 via REDCap (Research Electronic Data Capture; Vanderbilt University). Stratification based on the site of recruitment will be implemented. Due to the nature of ECEM-TZ, blinding will not be possible for mothers (ie, mothers will know if they receive text messages or not). To minimize bias at the participant level, all mothers will receive the same in-hospital care. Due to the nature of the intervention, mothers in the control group will not be exposed to the intervention text messages. Hospital staff (nurse midwives, physicians, and other health care providers) will be blind to participant group allocation to ensure both groups receive the standard discharge education. The researchers will be aware of participant allocation but will not be involved in data collection from participants or the randomization process. The research assistants will be blinded to allocation at baseline (T1) but not at T2.

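### The logistic model for the binary knowledge outcome takes its covariates from baseline significance tests, so it would almost always omit the stratification site and T1 knowledge, and no main model is named

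*Protocol article*

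**What the plan says.** All of this is in the protocol article.

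- **Sample Size.** "The sample size was calculated based on the outcome of newborn care knowledge", and in binary form: "we considered a binary summative score of 100% as the goal at 6 weeks post partum". The stated assumption is "assuming 90% of the intervention group and 70% of the control group will score 100% at 6 weeks", from which "a total sample size of 124 is required".
- **Randomization, Allocation, and Blinding.** "Stratification based on the site of recruitment will be implemented". Blocks vary from 4 to 8.
- **Outcome Measures, Table 1.** Newborn care knowledge is collected at T1 and at T2.
- **Statistical Analysis.** For scores: "Analysis of covariance will be used to measure whether scores differ between the two groups, adjusted for the pretest scores", together with any baseline characteristics found significant. For binary knowledge, morbidity, mortality and 6-week attendance: "binary variables will be created, and data will be analyzed using logistic regression". That sentence names no covariate.
- **Statistical Analysis, general rules.** Baseline characteristics that differ significantly between arms on a chi-square or Mann-Whitney test are to be adjusted for. Every analysis is to be reported both unadjusted and adjusted.

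Site appears as a covariate nowhere in the Statistical Analysis section.

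**The concern.** The same construct is treated in two ways. As a score, 6-week knowledge is adjusted for its T1 value. As the 100% binary outcome that justifies the sample size, it is adjusted only for whatever a baseline test happens to pick.

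That rule selects on the wrong property. A covariate helps when it predicts the outcome, whereas a baseline test only detects chance imbalance. In a properly randomised trial it picks each variable about 5% of the time whatever its prognostic value, and it picks a stratification factor practically never. The two variables with a design reason to be in the model are therefore the ones least likely to be there by plan.

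Two things are at stake: some precision on the outcome that drives the sample size, and a single result fixed in advance. With two versions reported and neither named as the main one, a split verdict would leave the reader without a rule for which to believe.

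**Working it through.** **1. The plan's own figure.** Inputs from Sample Size: p1 = 0.90, p2 = 0.70, two-sided α = 0.05, power 80%. Allocation is 1:1 and p̄ = 0.80. With pooled variance and no continuity correction:

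n per arm = [z(0.975)·√(2p̄(1−p̄)) + z(0.80)·√(p1(1−p1) + p2(1−p2))]² / (p1−p2)²

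= [1.960·√0.32 + 0.842·√0.30]² / 0.04 = (1.109 + 0.461)² / 0.04 = 61.6, rounded up to 62.

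The total is 124, an exact match. The formula has no covariates, so 124 is sized for an unadjusted comparison. Power is 80.3% at 62 per arm and 85.6% at the 71 and 72 recruited, before dropout.

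**2. Would the baseline test select site?** With blocks of at most 8, the arms can differ by at most 4 within a site. Assume sites of 72 and 71 (the protocol aims for similar numbers). The worst split consistent with arms of 72 and 71 is 38/34 at one site and 34/37 at the other:

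χ² = 143·(38·37 − 34·34)² / (72·71·72·71) = 143·250² / 5112² = 0.34, p about 0.56.

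Site would not be selected.

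**3. Would it select T1 knowledge?** Only if T1 knowledge counts as a baseline characteristic, and then in about 5% of properly randomised trials.

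**4. What adjustment would gain.** The document does not report how well T1 knowledge or site predicts the 6-week outcome, so both strengths are assumed over a range. Model: logit P = a + b·arm + g·X + s·site. X is a standard normal baseline score, there are two equal sites, allocation is 1:1 within site, and marginal rates are held at 70% and 90%. The test is a likelihood-ratio test, with 4000 runs per row.

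| N | g (log-odds per SD) | s (log-odds between sites) | Unadjusted | Site only | T1 only | Both |
|---|---|---|---|---|---|---|
| 124 | 0 | 0 | 82.2% | 82.3% | 81.6% | 81.8% |
| 124 | 0.5 | 0.5 | 82.9% | 83.0% | 83.2% | 83.7% |
| 124 | 1.0 | 0.5 | 82.6% | 82.7% | 86.7% | 87.1% |
| 124 | 1.0 | 1.0 | 82.7% | 83.4% | 87.0% | 87.8% |
| 124 | 1.5 | 0.5 | 83.0% | 83.1% | 90.7% | 91.0% |
| 143 | 0 | 0 | 87.5% | 87.5% | 87.4% | 87.4% |
| 143 | 0.5 | 0.5 | 87.1% | 87.3% | 87.8% | 88.2% |
| 143 | 1.0 | 0.5 | 87.2% | 87.5% | 91.1% | 91.5% |
| 143 | 1.0 | 1.0 | 86.4% | 87.2% | 90.6% | 91.7% |
| 143 | 1.5 | 0.5 | 88.0% | 88.2% | 94.2% | 94.3% |

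The gain from both covariates runs from about 0 to 8 points at N=124 and from about 0 to 6 at N=143. Site alone gives 0 to 1.

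**5. Type I error at N=124** (70% in both arms, 6000 runs). The unadjusted test rejected in 4.7% to 5.5% of runs, and the test adjusted for both in 5.4% to 5.9%. A separate latent-normal simulation with Wald tests gave 4.1% to 4.5% unadjusted and 4.9% to 5.3% adjusted. The small departures from 5% depend partly on the test statistic.

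**6. Room for covariates.** At the assumed rates, 62·0.30 + 62·0.10 = 24.8, so about 25 of 124 women miss the 100% score. The model can carry few covariates.

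**The case against.** A reader might infer that the binary outcome is to be analysed without adjustment. The text does not support that: the general rule promises an adjusted version of every analysis, the logistic ones included, and T1 knowledge could enter if it differed significantly. Baseline knowledge is also used for the same construct in the analysis of covariance of scores. What remains is narrower: the adjusted logistic model has no fixed covariates, and the stated way of choosing them would nearly always leave out both variables.

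A reader might also infer that the trial is underpowered for want of adjustment. It is not. The 124 was computed for an unadjusted comparison and delivers its 80%, and 143 women were randomised, although the numbers for analysis are not yet confirmed.

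It is fair to add that an article condenses the plan, and that a full covariate list is usually left to the analysis plan. That would answer a complaint about silence. Here the article states a selection rule, and the rule itself is the weakness.

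Finally, T1 is taken in hospital within about two days of birth and T2 by telephone six weeks later, so a strong association cannot be taken for granted. This stands, and it is why the range of gain starts at zero.

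**Conclusion.** The point holds as a matter of efficiency and prespecification. For the outcome that sizes the trial, covariates are chosen by baseline significance tests, the stratification factor is named in no model, and no main model is identified.

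The forgone power is about 0 points if T1 knowledge is not prognostic, about 4 to 5 at N=124 if it is moderately prognostic (1.0 log-odds per SD), and about 8 if strongly so (1.5 per SD). At N=143 the top of the range is about 6. These figures rest on assumed prognostic strengths and on the protocol's own 70% and 90%.

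Nearly all the gain comes from T1 knowledge. Site belongs in the model for consistency with the stratified randomisation, not for power. It might be inferred that leaving site out makes the test invalid or clearly conservative, but the simulated error rates do not show this.

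**What to change.** State one main analysis of the 100% knowledge outcome: logistic regression with arm, site and T1 knowledge score, saying which form of the score is used (for example the total count). Report the unadjusted model as supportive. Delete covariate selection by baseline significance tests and use these fixed covariates instead. Add site to each analysis of covariance, which already carries the pretest score.

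The cost is a sentence or two of analysis text and two parameters, with no new data: knowledge is already measured at T1, and site is known from the randomisation. The Figure 1 legend says that the analysis was not complete at publication. The change should be dated and made before outcomes are examined by arm. If they have already been examined, label the adjusted model as added afterwards.

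Optionally, report a standardised risk difference with its 95% confidence interval beside the odds ratio, because the trial was sized on a 20-point difference and an adjusted odds ratio differs from an unadjusted one even without imbalance. That is a reporting preference and not a correction.
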